## Abstract

**Introduction:**

Maternal diet during pregnancy has been linked to offspring allergy risk and it could represent a potential target for allergy prevention. The Mediterranean Diet (MD) is considered one of the healthiest dietary models. Randomized-controlled trials on the effect of MD in preventing pediatric allergic diseases are still needed.

**Methods and analysis:**

The Mediterranean Diet during Pregnancy study (PREMEDI) will be a 9-month multi-center, randomized-controlled, parallel groups, prospective trial. Healthy women (20–35 years) at their first trimester of pregnancy at risk for atopy baby, will be randomly allocated to Group 1 (standard obstetrical and gynecological follow-up and nutritional counseling to promote MD) or Group 2 (standard obstetrical and gynecological follow-up alone). 138 mother-child pair per group will be needed to detect a reduction in cumulative incidence of ≥1 allergic disease at 24 months of age. The primary study aim will be the evaluation of the occurrence of allergic disorders in the first 24 months of life. The secondary aims will be the evaluation of maternal weight gain, pregnancy/perinatal complications, growth indices and occurrence of other chronic disorders, mother-child pair adherence to MD and gut microbiome features, breastfeeding duration and breast milk composition, epigenetic modulation of genes involved in immune system, and metabolic pathways in the offspring.

**Ethics and dissemination:**

The study protocol has been approved by the Ethics Committee of the University of Naples Federico II (number 283/21) and it will be conducted in accordance with the Helsinki Declaration (Fortaleza revision, 2013), the Good Clinical Practice Standards (CPMP/ICH/135/95), the Italian Decree-Law 196/2003 regarding personal data and the European regulations on this subject. The study has been registered in the Clinical Trials Protocol Registration System.

**Clinical trial registration:**

[http://clinicaltrials.gov], identifier [NCT05119868].

## Introduction

### Background and rationale

Prevalence and severity of pediatric allergic diseases are increasing steadily in the last two decades under the pressure of environmental factors acting on genetically predisposed individuals (1). Innovative strategies aimed at limiting the pediatric allergy burden are advocated, to reduce the socio-economic costs for the families and the healthcare systems (1). The first 1,000 days of life, from the conception to 24 months, are crucial to achieve long-term health outcomes and represent a strategic period to intervene under prevention and public health perspective (2).

Nutritional exposures during this critical period of life can influence the future disease susceptibility (3). Maternal diet during pregnancy has been linked to offspring allergy risk and it could represent a potential target for allergy prevention (1). The Mediterranean Diet (MD) is considered one of the healthiest dietary models, which impacts beneficially the gut microbiome (GM), providing high amounts of fiber, antioxidants polyphenols and vitamins, and a balanced ratio of essential fatty acids (ω6:ω3) (4). Notably, the MD beneficial effects are due to the synergistic and interactive combinations of nutrients, and the modulation of gene expression through epigenetic changes is one important mechanism by which MD can lead to regulatory effects in immune system (5). Advances in understanding diet-GM-epigenetics-immune system axis have highlighted the importance of GM-derived metabolites in maintaining health and immune homeostasis. Among the GM-derived metabolites, the short-chain fatty acids (SCFAs) have emerged as key signaling molecules driving beneficial downstream effects on immune pathways (6). MD is typified by a high-level of whole cereals, fruit, vegetables, and legumes, the main fermentation substrates for SCFAs microbial production (4). In addition, overall MD-derived components, like ω-3 long chain poly-unsaturated fatty acids such as eicosapentaenoic and docosahexaenoic acids derived from marine foodstuffs, mono-unsaturated oleic acid of olive oil (rich in antioxidants e.g., tocopherols), vitamins and trace elements, polyphenols and carotenoids including lycopene, are known for their anti-inflammatory and anti-allergic capacities, indicating their potencies to improve allergy protection by combining these elements (7).

Although, several observational birth-cohort and retrospective studies have provided conflicting results on the effects of MD in pregnancy on allergy prevention in the offspring. Eight studies have explored the effect of maternal MD during pregnancy on the incidence of allergic diseases in the offspring (8–15). Six of them were cohort studies (8–13), and two were cross sectional studies (14, 15). In the ALSPAC (Avon Longitudinal Study of Parents and Children) birth cohort study adherence to MD during pregnancy was not associated with a reduced risk of asthma or other allergic outcomes in the offspring but may be associated with increased small airway function in childhood (13). Similarly, a study involving 1,087 Spanish infants from the International Study of Wheezing in Infants (Estudio Internacional de Sibilancias en Lactantes, EISL) showed that the consumption of MD during pregnancy did not elicit protective effect for wheezing, recurrent wheezing, or eczema at 12 months of age in children (11). Another Spanish observational study did not evidence any association between maternal adherence to the MD and development of wheezing, rhinitis, and dermatitis in the children at 4 years of age (15). Likewise, the results of a USA pre-birth cohort of 1,376 mother-infant pairs from Project Viva showed that MD during pregnancy was not associated with recurrent wheeze at 3 years of age (12). Furthermore, a high adherence to MD during pregnancy was not significantly associated with reduction of infantile wheeze or eczema in two mother-child cohorts in Spain and Greece (10). On the contrary, two Spanish studies reported that high adherence to MD during pregnancy elicited significant negative associations with wheeze and atopy in children (8, 9), and one study from Mexico reported that adherence to MD was inversely associated with asthma, wheezing, rhinitis, sneezing, current sneezing, and current itchy-watery eyes (14). Lastly, a general low MD-adherence has been described during pregnancy (16). These data were confirmed by the results of a pilot study performed at our Center, where we observed a low adherence rate to MD in pregnant women at their first trimester of pregnancy (unpublished data).

Unfortunately, these studies have assessed maternal diet retrospectively. Thus, the lack of prospective randomized-controlled trials, exploring the effects of a specific nutritional counseling for MD promotion during pregnancy on allergy prevention in the offspring, is a major limitation for understanding the role of MD in pregnancy in preventing pediatric allergies. The Mediterranean Diet during Pregnancy study (PREMEDI) was designed to address this limitation.

Whilst previous studies provided conflicting results on the protective effect elicited by MD against pediatric allergies, it is unknown whether an intervention to promote the MD in pregnancy could reduce the likelihood of allergic diseases in the offspring. We hypothesize that a dietary intervention aiming to promote an optimal adherence to MD during pregnancy could be able to limit the occurrence of allergic diseases in early childhood, including atopic eczema, allergic oculorhinitis, allergic urticaria, asthma, and IgE and non-IgE mediated food allergies.

## Methods and analysis

### Study settings

The study will involve four tertiary gynecology and neonatology centers located in the Campania region in Italy. The annual number of births at each center is >1,500.

### Study design

The PREMEDI Study will be a 9-month multi-center, randomized-controlled, parallel groups, prospective trial.

The study will involve three parallel teams: Research Team (RT), Clinical Team (CT), and Statistical Team (ST). The RT will be composed by physicians, molecular biologists, and dietitians. The CT will be composed by gynecologists, neonatologists, pediatricians, family pediatricians, allergologists, dietitians, and pediatric nurses. The ST will be composed by statisticians. A Study Monitor will overview the trial’s data management and analysis.

The RT will be dedicated to the enrollment and the randomization of participants. Then, the dietitians of the RT will perform the personalized nutritional counseling during the study phases. The CT will evaluate the participants and will collect data in anonymous form and will deliver data to the ST. The ST, unaware of study cohorts, will review the study dataset and will undergo data cleaning and verification according to standard procedures. Finally, ST will lock the database once it will be declared complete and accurate and will perform statistical analysis.

The graphical representation of study design is reported in Figure 1.

**FIGURE 1 F1:**
[figure not shown]
The study design. The figure shows a graphical representation of the study design, including the set of procedures at each study visit, and including the execution team.

The Figure 2 reports the participant flow through the study.

**FIGURE 2 F2:**
[figure not shown]
The study participants flow. The figure shows the flow of the participants through the study.

In the Figure 3 is depicted the study plan.

**FIGURE 3 F3:**
[figure not shown]
The study plan. The figure show the time schedule of screening, intervention, and follow-up.

### Eligibility criteria

We will consider for the study all healthy women (aged 20–35 years) attending their first pregnancy visit at 8–13 gestational weeks (GW) consecutively observed at the four centers. We will consider only pregnant women with a pregnancy of at risk for atopy baby. The atopy risk will be defined by the presence of at least one first degree family member of the baby with documented history of allergic diseases. We will exclude from the study all women aged <20 and >35 years, or with concomitant presence of infections, malignancies, major gastrointestinal malformations, immunodeficiencies, autoimmune diseases, chronic inflammatory bowel diseases, pre-existing diabetes, chronic renal disease, celiac disease, history of abdominal surgery with gastrointestinal resection, neurologic and neuropsychiatric disorders, genetic and metabolic disorders, vegan diet, twin pregnancy.

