### Allocation and blinding

The randomization and sequence allocation will be performed according to a computer-generated randomization list by building a stratified randomization with permutated block-randomization, stratified by maternal body mass index (BMI) (<25, 25–29.9, and ≥30 kg/m^2^), and parity (1 or >1), in an allocation ratio of 1:1 in blocks of 4–6. The Group #1 will receive standard obstetrical and gynecological follow-up and nutritional counseling to promote MD provided by certified dietitians, and the Group #2: will receive standard obstetrical and gynecological follow-up alone. Due to the nature of the RCT design, participants and RT will be aware of the group assignment. Whereas the allocation to Group #1 or Group #2 will remain unknown to the CT and ST.

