### Data and sample collection

At baseline, after the first evaluation by the RT and the collection of written informed consent form, the CT will collect the following variables in a dedicated chart: anamnestic and clinical features, personal and anthropometric data, socio-demographic factors, gestational age, allergies, number of cohabitants, pets, sports activities, use of drugs, smoking exposure, education level, family and living conditions. At enrollment a validated questionnaire on MD-adherence (Med Diet Score) and a 7-day food diary (five weekdays and two weekend days) will be collected. The 7-day food dairy data will be analyzed using specific software (Winfood–Medimatica Srl) by a dietitian. The intake of drugs, dietary supplements, pre-, pro-, and synbiotics will be recorded in the same chart. Then, the RT will schedule for each participant follow-up visits every 12 weeks from the enrollment (8–13 GW), then at 14–28 GW and at 29–40 GW. During these visits the CT will perform a full physical examination, anamnestic and clinical data collection, stool sampling (at least 3 g), 7-day food diary collection, Med Diet Score assessment. Each item assigns a score of 0 or 1, with a total score ranging from 0 to 14. The three categories of adherence to MD are divided in ≤5 (low), 6–9 (medium), ≥10 (high) score. Furthermore, to ensure and encourage the completion of the 7-day food diary, one week before each visit, the RT will remind the women by a phone call to fill in the food diary daily for the following week and to return them at the following visit. At delivery a cord blood sample (at least 10 ml) and a breast milk sample (collected within 24 h after delivery) (3 ml) will be collected. All neonatal clinical features will be evaluated by CT. After delivery, for all babies a follow-up visit will be planned every 3 months for the first 12 months of life and then every 6 months until the age of 2 years. At each visit the following procedures will be adopted by CT: full anamnestic and clinical evaluation, body growth assessment, occurrence of allergic disorders, occurrence of other conditions, 7-day food diary, child Mediterranean Diet Quality Index score (KIDMED) evaluation, stool sampling (at least 3 g). At each visit the persistence of breastfeeding will be also assessed and a breast milk sample will be eventually collected (3 ml). In addition, Skin Prick Testing using main pediatric allergens will be performed at 12 and 24 months. All collected data and documents will always remain confidential.

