### Sample size calculation

Based on the results of the EUROPREVALL cohort (29), reporting a cumulative incidence for allergic diseases of 30%, and on the results of a previous pilot study performed at our center (unpublished data) showing a drop-out rate to this kind of intervention up to 15%, we estimated that 138 mother-child pair per group will be needed to detect a reduction in cumulative incidence of at least one allergic disease at 24 months from 30 to 15%, with a power of 0.80 at an alpha level of 0.05 (Pearson’s Chi-square, two-tailed test).

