### Statistical methods

All data will be collected in a dedicated database and analyzed by the ST. We will perform intention to treat (ITT) and per-protocol analysis. We will perform ITT analysis by considering the mother-child pair lost after randomization: (1) all missing values of the primary outcome will set to the worst outcome in both groups (equal-case scenario ITT) and (2) missing values of the primary outcome will set to the worst outcome in the Group 1 and to the best outcome in the Group 2 (worst-case scenario ITT). The worst outcome will be defined as the occurrence of ≥1 atopic condition at 24 months, in the offspring; the best outcome will be its opposite. The secondary outcomes will be evaluated using per-protocol analysis. The Kolmogorov-Smirnov test will be used to determine whether variables are normally distributed. Descriptive statistics will be used to summarize baseline characteristics. The Student *t*-test will be used to compare mean values of continuous variables for approximating a normal distribution. For non-normally distributed variables, the Mann-Whitney *U* test will be used. The χ^2^ test or Fisher exact test will be used, when appropriate. We will use a binomial regression model (BRM) to estimate the incidence of the main outcome, i.e., at least one atopic condition at 24 months, in the offspring. The response variable of the BRM will be the presence of at least one atopic condition at 24 months (0 = no; 1 = yes), and the predictor will be the treatment cohort (0 = Group 1; 1 = Group 2). To evaluate the effect of potential confounders on the main outcome, we will add each of them separately to the aforementioned BRM and we will evaluate the changes in the estimated risk ratios. The evaluated potential confounders will be sex (0 = female; 1 = male), age (months), cesarean delivery (0 = no; 1 = yes), born at term (0 = no; 1 = yes), breastfed for at least 2 months (0 = no; 1 = yes), weaning (months), siblings (number), exposed to passive smoking (0 = no; 1 = yes), mother smoked during pregnancy (0 = no; 1 = yes), and exposed to pets (0 = no; 1 = yes), drug use (0 = no; 1 = yes), antiseptics exposure (0 = no; 1 = yes), lifestyle (0 = rural; 1 = urban), dietary habits (0 = low MD-adherence; 1 = medium MD-adherence; 2 = high MD-adherence) and pollution exposure (0 = no; 1 = yes). BRM is among the most commonly suggested methods to report the results from randomized controlled trials with binary outcomes. Regression modeling allows adding baseline co-variables to increase the precision of the estimate and better control for potential confounders. Comparisons of taxa or gene abundance between groups will be carried out using pairwise Wilcoxon tests. Statistical significance of pangene prevalence will be verified through Fisher’s test with multiple-hypothesis testing corrections *via* the false discovery rate (FDR). Machine learning-based classification analysis will be done using the MetAML package (30) and by considering random forests (RFs) as back-end classifier for all the results. Results will be obtained through a fivefold cross-validation and averaged on 20 independent runs. To evaluate whether the significant associations for the cord blood analysis primarily reflect maternal adherence to MD, additional models adjusted for cord blood DNA methylation of the same CpG site and for miRNAs will be evaluated when examining the association between DNA methylation/miRNAs and childhood allergic sensitization. For DNA methylation, using a reference methylation Quantitative Trait Loci (QTL) library, we will evaluate the genetic control of methylation for the top 30 associated CpG sites identified from the mid-childhood meta-analysis for atopic sensitization, environmental and food allergen sensitization. We leveraged genetic-epigenetic information from the ARIES large-scale genome-mQTL analysis, which included 1,000 mother-child pairs^2^ (31). mQTL comparisons will be focused on the *cis* position (i.e., a genetic variant within ±500 Kb of a methylation locus) measured from cord blood, and with MAF ≥5%. The level of significance for all statistical tests will be two-sided, *p* < 0.05. An integrative approach that combines multi-omics data together with integrated clinical data analysis will be performed. Multivariable linear regression will be used to analyze associations differentially methylated regions in cord blood DNA with clinical measures of offspring. All significance values will be corrected to take into account the effect of multiple comparisons, using the Bonferroni adjustment. All analyses will be performed with Stata 16.1 (Stata Corporation, College Station, TX, USA), SAS^®^ version 9.4 (SAS Institute, Inc., Cary, NC, USA) and R version 3.4.1.

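### Variation in family atopy beyond the entry threshold is neither stratified on nor named as a covariate, a small and cheaply repaired loss of precision

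*Protocol article*

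**What the plan says.** All of this is in the protocol article.

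- **Eligibility criteria.** The child's risk is defined by family history alone: "The atopy risk will be defined by the presence of at least one first degree family member of the baby with documented history" of allergic disease. The threshold is not graded by number of relatives, by which relative, or by disease.
- **Allocation and blinding.** The list is "stratified by maternal body mass index (BMI", in three bands) and by parity. Family atopy is not a stratum.
- **Data and sample collection.** The baseline chart includes "socio-demographic factors, gestational age, allergies, number of cohabitants" and other items. It does not say whose allergies are meant or whether allergic relatives are counted.
- **Statistical methods.** The primary binomial regression has treatment as its only predictor. Named variables are then added one at a time to see how the risk ratio moves: "The evaluated potential confounders will be sex (0 = female; 1 = male), age (months), cesarean delivery" and twelve more, fifteen in all. They include pets, antiseptics, urban or rural lifestyle and pollution, but not family or maternal atopy. The same section justifies regression by the precision and the control of confounding that baseline variables can bring.

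**The concern.** The trial selects on family atopy, so it must establish at least part of this factor before randomisation. Yet the factor drops out of both the design and the analysis. At least four of the fifteen listed covariates (cesarean delivery, birth at term, breastfeeding, weaning) arise after randomisation. They serve the section's stated purpose for baseline variables less well than a pre-randomisation risk factor would.

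Family history also enters the outcome definitions. In the section on allergic disorders in the offspring, family atopic history is one of the four major eczema criteria, and asthma in first-degree relatives counts towards an asthma diagnosis. Which disease a relative has may therefore bear on whether a child is counted as a case.

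At stake is how far a chance difference between groups in allergic family load could move the one realised result, and how much precision is given up by not using the factor.

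**Working it through.** **1. The plan's sample size.** Inputs from the Sample size calculation section: a "reduction in cumulative incidence of at least one allergic disease at 24 months from 30 to 15" per cent, "with a power of 0.80 at an alpha level of 0.05 (Pearson’s Chi-square, two-tailed test"), and a pilot "showing a drop-out rate to this kind of intervention up to 15" per cent. The stated result is "we estimated that 138 mother-child pair per group will be needed".

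- Unpooled variance: (1.960 + 0.842)² × (0.30×0.70 + 0.15×0.85) / 0.15² = 7.849 × 0.3375 / 0.0225 = 117.7, so 118. Then 118/0.85 = 138.8, so 139.
- Pooled variance: 121, giving 143 after division by 0.85, or 140 after multiplication by 1.15.

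The figure of 138 is reproduced to within one pair by the unpooled formula and is not in dispute. Expected completers: 138 × 0.85 = 117 per group.

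**2. Assumptions.** The documents give neither the share of children with a stronger family history nor its effect. I take a binary factor with prevalence q = 0.3–0.5 and risk ratio RR = 1.5–2.5. The control risk of 30% comes from the protocol.

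**3. Chance imbalance.** SD of the between-group difference in prevalence = √(2q(1−q)/117).

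- q = 0.3: √(0.42/117) = 0.060, 95% limit 11.7 points.
- q = 0.5: √(0.50/117) = 0.065, 95% limit 12.8 points.

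The probability of an imbalance above 10 points is 10–13%.

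**4. Shift in the risk difference.** Risk in the lower stratum is p₀ = 0.30/(1 − q + q·RR), and the gap between strata is p₀(RR − 1). With no treatment effect, shift = imbalance × gap. If Group 1 has half the risk in each stratum (15% overall), its gap is also halved. With the imbalance spread evenly around q, the shift is then 0.75 × imbalance × gap.

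**5. Power.** Simulated with 40,000 trials per setting and 117 per group, 30% versus 15%. The unadjusted test is compared with a Cochran-Mantel-Haenszel test stratified on the factor.

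| q | RR | Gap | Shift, no effect (points) | Shift, planned effect (points) | Power unadjusted → adjusted (%) |
|---|---|---|---|---|---|
| 0.3 | 1.5 | 0.130 | 1.5 | 1.1 | 79.6 → 79.9 |
| 0.3 | 2.0 | 0.231 | 2.7 | 2.0 | 79.2 → 80.4 |
| 0.3 | 2.5 | 0.310 | 3.6 | 2.7 | 79.3 → 81.9 |
| 0.5 | 1.5 | 0.120 | 1.5 | 1.2 | 79.3 → 79.5 |
| 0.5 | 2.0 | 0.200 | 2.6 | 1.9 | 79.4 → 80.3 |
| 0.5 | 2.5 | 0.257 | 3.3 | 2.5 | 79.4 → 81.3 |

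The simulation error of each power figure is about 0.2 points (√(0.8×0.2/40,000)). Simulated type I error for q = 0.3–0.5 was 4.9–5.2% unadjusted and 4.9–5.1% adjusted.

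**6. Scale.** Under the planned effect, the standard error of the risk difference is √(0.3375/117) = 5.4 points, so the largest shift, 2.7, is 0.5 SE. With no effect it is √(0.42/117) = 6.0 points, and 3.6 is 0.6 SE.

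**The case against.** The strongest reply is that randomisation already deals with this. The test and confidence interval allow for chance imbalance, which is as likely to hide an effect as to exaggerate one. An unadjusted primary analysis of a randomised trial is legitimate, and no sentence in the protocol is false here. All of that stands. A reader might infer that the primary comparison is biased, or that a counselling effect could not be told apart from an unlucky allocation. The documents do not support this: type I error is unaffected, and the plan does provide for a summary of baseline characteristics.

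A reader might also infer that the trial ignores its main risk factor. The protocol does not rank family history in that way. What it uses to define risk, at least one allergic relative, is met by every child and cannot be imbalanced. Only the variation above that threshold can be, and its strength is my assumption.

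Nor do the documents show that the number of allergic relatives is recorded. Screening could stop at the first documented one, and the baseline chart says only allergies.

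Finally, the parity stratum and the siblings covariate touch part of the variation in the number of relatives, though not parental atopy.

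The omission itself remains. The Statistical methods section names its covariates explicitly, so this is a choice the protocol fixes and not a detail left to an analysis plan. It also fits poorly with the reason the section gives for using baseline variables.

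**Conclusion.** The point holds as a minor one. The plan leaves unused a pre-randomisation factor that it partly establishes at entry. The cost is 0.2 to 2.6 points of power. An imbalance at its 95% limit would shift the risk difference by about 1.1–2.7 points under the planned effect, or 1.5–3.6 points under no effect. By definition only about one trial in twenty would have an imbalance that large or larger. The validity of the primary test is not in question.

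These sizes rest on an assumed prevalence of 30–50%, an assumed risk ratio of 1.5–2.5, and 117 completers per group. With a weaker gradient the gain would be negligible.

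**What to change.** In the Statistical methods section, pre-specify a family-atopy term before unblinding. Code it from the eligibility and baseline record: mother allergic, yes or no, and, where recorded, one versus two or more allergic first-degree relatives. Enter it together with treatment in the primary binomial regression, report the unadjusted risk ratio alongside, and tabulate the factor by group at baseline.

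Adding it to the existing list would not be enough. Those variables enter singly, as a check on the risk ratio, and leave the primary estimate unchanged. Adjustment does not change what is being estimated if the risk ratio is the same at each level of the factor. No change to the randomisation is needed.

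The cost is one or two model terms and, if the number of allergic relatives is not already captured, possibly one added item on the case report form.
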